### Withdraw criteria

1. Unable to tolerate the clinical trial and requesting an early withdrawal. 2. Patient is unsuitable for further trials due to deterioration. 3. Poor compliance with the follow-up plan.

### Sample size

The sample size is calculated using the Contingency Table (Chi-Square Tests) in the PASS 15.0 software. A literature review showed that nCPAP was approximately 65% effective for neurological recovery in stroke patients and 55% effective for HFNC, compared to 40% in the standard oxygen therapy group [14, 15]. In this study, the test level α = 0.05 and the test efficacy 1-β = 0.9. The final sample size is expected to be 150 cases, considering a 10% loss to follow-up rate, including the possibility of deterioration after admission and loss to follow-up after discharge.

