**Methods:**

This randomised controlled study will be conducted in the intensive care unit of the Department of Neurology at the Wuhan Union Hospital. According to the study plan, 150 patients with sleep apnea after AIS will be recruited. All patients are randomly allocated in a 1:1:1 ratio to one of three groups: the nasal catheter group (standard oxygen group), the HFNC group, and the nCPAP group. Patients receive different types of ventilation after admission to the group, and their tolerance while using the different ventilation is recorded. Patients will be followed up by telephone three months after discharge, and stroke recovery is recorded. The primary outcomes were 28-day mortality, the incidence of pulmonary infection and endotracheal intubation.

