### Study outcomes

#### Primary outcomes

1. 28-day mortality rate; 2. Tracheal intubation rate (Rate of tracheal intubation in each group after one week using different ventilation methods); 3. Pulmonary infection rate (Rate of pulmonary infections in each group after one week using different ventilation methods).

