#### Secondary outcomes

1. National Institute of Health stroke scale (NIHSS). The NIHSS is used to evaluate the severity of stroke patients. Changes in NIHSS scores after one week in acute ischemic stroke patients with different ventilation modes. NIHSS scores range from 0–42, with higher scores indicating more severe neurological damage. 2. Barthel index. The Barthel index is used to assess the ability of stroke patients to live independently. This study assesses whether the quality of life of patients with acute ischemic stroke improves at one month and three months. 3. Sleep apnea symptoms. To assess changes in sleep apnea symptoms in patients with acute ischemic stroke. After one week of treatment with different ventilation modalities, polysomnography will be performed again to assess whether sleep has improved in stroke patients by calculating the magnitude of the AHI value. The minimum value of the AHI is 0, and there is no maximum value. A higher AHI value indicates more severe sleep apnea symptoms; 4. Time of hospitalization; 5. Cost of hospitalization; 6. Neurological recovery (mRS).

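### The only power calculation is for a secondary outcome, so the stated 90% applies to none of the three primary outcomes; on its own inputs it fails for the secondary outcome too

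*Protocol article*

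**What the plan says.** The Sample size section of the protocol article names its method: "The sample size is calculated using the Contingency Table (Chi-Square Tests) in the PASS 15.0 software". It then gives the only rates used anywhere for sizing. The first is for nCPAP: "A literature review showed that nCPAP was approximately 65% effective for neurological recovery in stroke patients". The rates for the other two arms follow: "55% effective for HFNC, compared to 40% in the standard oxygen therapy group". The error rates are "In this study, the test level α = 0.05 and the test efficacy 1-β = 0.9", and the result is "The final sample size is expected to be 150 cases, considering a 10% loss to follow-up rate". The abstract fixes equal allocation: "All patients are randomly allocated in a 1:1:1 ratio to one of three groups". That is 50 per arm, or about 45 per arm after 10% loss.

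The Primary outcomes section lists "28-day mortality rate; 2. Tracheal intubation rate (Rate of tracheal intubation in each group after one week using different ventilation methods"), followed by the pulmonary infection rate at one week. The abstract names the same three. "Neurological recovery (mRS") is the sixth and last item under Secondary outcomes. The Discussion mentions neurological recovery alongside the three primaries as something to be compared, but does not reclassify it. The Statistical analysis section plans chi-square tests for categorical variables.

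**The concern.** A sample-size statement tells readers what the trial can detect on the outcomes that decide it. Here the statement concerns an outcome that does not decide it. The outcomes that do have no assumed control rate, no target difference and no power.

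The abstract's Discussion says that the trial will investigate whether nCPAP and HFNC reduce early mortality and intubation. If those comparisons come out non-significant, the only power figure a reader can attach to them is 90%. A result that may carry little information could then pass for evidence of no effect from an adequately powered trial.

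The article does state a basis for its sample size, and that basis is an outcome from the wrong tier. This is therefore not a detail that an article could be expected to leave to the full protocol or to an analysis plan.

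**Working it through.** **1. Reproducing the plan's own figure**

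Inputs from the Sample size section: rates 0.65, 0.55 and 0.40; alpha 0.05; power 0.90; total 150 with 10% loss, so 150 × 0.9 = 135 evaluable. Three arms and a binary outcome give a 3×2 chi-square test with 2 degrees of freedom.

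- Mean rate: (0.65 + 0.55 + 0.40)/3 = 0.5333.
- Effect size: W² = mean of (pᵢ − p̄)², divided by p̄(1 − p̄). The squared deviations are 0.01361, 0.00028 and 0.01778, with mean 0.01056. Dividing by 0.5333 × 0.4667 = 0.2489 gives W² = 0.0424 (W = 0.206).
- Noncentrality is N × W². For 90% power at alpha 0.05 with 2 df it must reach 12.65, so N = 12.65/0.0424, or about 299 evaluable. Allowing for 10% loss, 299/0.9 gives 333 enrolled.
- With N = 135, noncentrality is 5.73 and power is 56%. With N = 150, it is 6.36 and power is 61%. Simulation gives 57% and 61%.

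The stated 150 is not reproduced. Variants tried were 1 df, alpha 0.10, a goodness-of-fit form, and pairwise tests one- and two-sided with and without continuity correction. At 90% power none needs fewer than about 201 evaluable (224 enrolled). For comparison, pairwise two-sided power at 50 per arm is 71% for 65% vs 40%, 32% for 55% vs 40%, and 17% for 65% vs 55%.

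**2. Primary outcomes**

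The document gives no event rates, so the control rates and effects below are assumptions. The test is the same 3×2 chi-square. Simulated power:

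| Control / HFNC / nCPAP | 45 per arm | 50 per arm |
|---|---|---|
| *Both active arms halve the risk* | | |
| 10 / 5 / 5% | 13.6% | 15.3% |
| 20 / 10 / 10% | 27.4% | 30.0% |
| 30 / 15 / 15% | 42.3% | 46.5% |
| 40 / 20 / 20% | 58.7% | 63.5% |
| *nCPAP halves the risk, HFNC achieves half of that reduction* | | |
| 10 / 7.5 / 5% | 10% | 12% |
| 20 / 15 / 10% | 20% | 22% |
| 30 / 22.5 / 15% | 31% | 34% |
| 40 / 30 / 20% | 45% | 49% |
| *Very large effects* | | |
| 30 / 15 / 5% | 85% | 89% |
| 40 / 20 / 10% | 88% | 92% |

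The noncentral chi-square formula agrees within about 4 percentage points. By that formula, total evaluable N for 90% power when both active arms halve the risk is 1,418 at a 10% control rate, 659 at 20%, 405 at 30% and 279 at 40%.

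**The case against.** The strongest reply is that the document does not establish that power for the primaries is low. A reader might infer from the mismatch that true power for mortality, intubation and infection is far below 90%. That goes further than the text allows. No event rates are given, and at 30/15/5% or 40/20/10% the planned size yields roughly 85–92%. Eligibility (NIHSS 2–20, GCS at least 9, preserved cough) suggests infrequent deaths and intubations. But the setting is an intensive care unit, and the document offers no such argument for pulmonary infection. This objection stands: low power is conditional on moderate effects.

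A reader might also conclude that 90% power is unattainable at control rates of 15% or below. That comes from a normal approximation. Enumerating the uncorrected two-group chi-square at 45 per arm gives about 92% for a fall from 15% to 0%, although removing every event is not a credible planning target.

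A third reply is that the section openly names neurological recovery, so nobody need be misled. That is fair as to disclosure. It does not supply a power basis for the primaries, and it does not rescue the 90% figure for recovery.

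Finally, one-week outcomes may suffer less loss than three-month follow-up, which favours 50 per arm over 45. Both are shown, and the conclusion is the same.

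**Conclusion.** The mismatch holds on the face of the document: the stated 90% power belongs to a secondary outcome and to none of the three primaries, whose power is unstated and cannot be derived from the document.

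If the true effect is a halving of risk in both active arms, power is about 14–15% at a 10% control rate, rising to 59–64% at 40%. It is lower if HFNC does less than nCPAP, and it approaches 90% only for very large effects. These figures rest on assumed rates, an omnibus chi-square test at 5% for each outcome taken alone, and 45 to 50 patients per arm.

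The mismatch might also tempt a reader to infer that 90% is at least right for neurological recovery. It is not. On the section's own inputs power is about 56–61%, and 90% would need about 299 evaluable patients. This part needs no outside assumption beyond reading the named method as a 3×2 test.

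**What to change.** In the Sample size section:

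- Withdraw the 90% figure.
- State that 150 was derived for the secondary outcome neurological recovery, and that on the stated rates it gives about 56% power (135 evaluable) to 61% (150).
- State that the three primary outcomes were not powered.
- Add a short table of the detectable difference for each primary outcome at 45 to 50 per arm, over a stated range of control rates.
- Commit to reporting the primaries as estimates with confidence intervals, so that a non-significant result is not read as evidence of no effect.

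Do not promote neurological recovery to primary. It would still have only about 56–61% power. The trial is open-label, and the planned recruitment period (to the end of April 2023) precedes the article's publication on 6 June 2023, so a switch then would itself be open to challenge. A change that affects the conduct of the study would also need ethics approval under the Modification of the protocol section.

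The cost is wording and one table, with no extra patients. The downside is that the stated power looks less favourable.

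### The printed inputs (65%, 55%, 40%; α 0.05; 10% loss) give about 56% power with 150 patients, not the stated 90%

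*Protocol article*

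**What the plan says.** The Sample size section of the protocol article gives a full set of inputs and a result.

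- Test: "The sample size is calculated using the Contingency Table (Chi-Square Tests) in the PASS 15.0 software".
- Assumed rates: "nCPAP was approximately 65% effective for neurological recovery in stroke patients and 55% effective for HFNC", "compared to 40% in the standard oxygen therapy group".
- Error rates: "the test level α = 0.05", with "the test efficacy 1-β" set at 0.9.
- Result: "The final sample size is expected to be 150 cases, considering a 10% loss to follow-up rate".

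The abstract and the section on study design and setting fix 1:1:1 allocation, so 150 means 50 per arm. The Statistical analysis section plans chi-square tests for categorical variables, which agrees with the test used for sizing.

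**The concern.** Rates of 65%, 55% and 40% are only moderately far apart, and 50 patients per arm is few for separating them with 90% power. Since every input is printed, the total can be checked without any outside figure.

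The power statement governs how a null result is read. If power is 90%, failing to find a difference is fair evidence against the assumed effect. If it is near 56%, such a failure is almost as likely as not even when the assumed effect is real. HFNC, the newer treatment, would suffer most, because its assumed rate lies between the other two and its pairwise contrasts are the weakest.

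**Working it through.** **Inputs** (Sample size section, plus the 1:1:1 allocation): p = 0.65, 0.55, 0.40; equal arms; α = 0.05; target power 0.90; 10% loss; total 150. A 3 × 2 table has df = 2, and its test has no direction. Evaluable patients: 150 × 0.90 = 135, or 45 per arm.

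**Effect size**

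- Mean rate p̄ = (0.65 + 0.55 + 0.40)/3 = 0.5333
- Mean squared deviation = (0.1167² + 0.0167² + 0.1333²)/3 = 0.010556
- p̄(1 − p̄) = 0.24889
- w² = 0.010556/0.24889 = 0.04241, so w = 0.206

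**Attempt to reproduce 150.** The noncentrality is λ = N·w², and the critical value is the 95th percentile of chi-square on 2 df.

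| Target power | λ needed | Evaluable N = λ/w² | Enrolled = N/0.90 |
|---|---|---|---|
| 90% | 12.654 | 298.4, so 299 | 331.5, so 332 |
| 80% | 9.635 | 227.2, so 228 | 252.4, so 253 |

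Neither row gives 150. Rounded up to equal arms, the 90% figure is 333.

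**Power that 150 does give**

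| Evaluable N | λ = N × 0.04241 | Power, noncentral chi-square | Power, simulation |
|---|---|---|---|
| 135 | 5.73 | 56.3% | 56.5% |
| 150 | 6.36 | 61.1% | 61.3% |

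The simulation agrees with the formula, so the approximation does not explain the gap.

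**Effect size that 150 would require.** For 90% power, w = √(12.654/135) = 0.306, or √(12.654/150) = 0.290 with no loss. The printed rates give 0.206.

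**Pairwise power at 45 per arm**, two-sided 0.05, no multiplicity adjustment:

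Power = Φ{ [d√n − 1.96√(2p̄q̄)] / √(p₁q₁ + p₂q₂) }, where d is the difference between the two rates, p̄ is their mean and q = 1 − p.

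- nCPAP vs standard: (1.677 − 1.384)/0.684 = 0.428, giving 67%
- HFNC vs standard: (1.006 − 1.384)/0.698 = −0.541, giving 29%
- nCPAP vs HFNC: (0.671 − 1.358)/0.689 = −0.997, giving 16%

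**Other readings tried, all at 90% power and three arms**

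| Reading | Evaluable | Enrolled |
|---|---|---|
| df = 1 instead of 2 | 248 | 276 |
| α = 0.10, df = 2 | 247 | 275 |
| Sized on 65% vs 40% only, two-sided | 246 | 274 |
| Sized on 65% vs 40% only, one-sided | 201 | 224 |

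A trend test across the three arms has 67% power two-sided, or 78% one-sided, at 45 per arm.

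Two calculations do land near 150. A one-sided, two-group comparison of 65% with 40% at 90% power needs 67 per arm, 134 in total, or 149 after loss. That is about 75 per arm in two arms and leaves HFNC out. The same contrast at 80% power, one-sided, gives 147 for three arms with no allowance for loss, which contradicts both the stated power and the stated loss.

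**The case against.** Nobody outside the team can see what was entered in PASS. The article is condensed: it does not print w, the degrees of freedom or the contrast, and it calls the rates approximate. Power is sensitive to them. At 70%, 60% and 35% (each rate moved by 5 points), w is 0.296 and power with 135 evaluable is 88%. Strictly, then, the check shows that the printed inputs and the printed total disagree; it does not show which is wrong. That limit stands, and it shapes the correction. It does not remove the error, because the section as published is internally inconsistent whichever part is at fault. A generic medium effect of w = 0.3 does not rescue it either: 12.654/0.09 = 140.6, so 141 evaluable, or 157 enrolled.

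A second objection is about scope, and it is fair. The rates concern neurological recovery, which the article lists as a secondary outcome (mRS). The primary outcomes are 28-day mortality, intubation and pulmonary infection. Neither 90% nor 56% describes the power for any of those, so a corrected figure must name its endpoint.

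Third, the plan promises no pairwise power, so those figures are additions and not corrections. They are still useful, since the article's questions about HFNC are pairwise ones. Lastly, recruitment was scheduled to end before the article appeared, so only the wording can change. That limits the remedy but does not excuse the claim.

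**Conclusion.** The concern holds. Under the plan's own rates, test, α and loss, 150 patients give about 56% power for the three-group comparison of neurological recovery (61% with no loss), a shortfall of about 34 percentage points from the stated 90%. The enrolment needed for 90% is about 332, more than twice the planned number.

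This rests on three things: a 3 × 2 table with equal arms and df = 2, the printed rates taken at face value, and 10% loss spread evenly over the arms. No alternative reading that keeps three arms, 90% power and 10% loss comes near 150. The result says nothing about power for the three primary outcomes. The statement must be corrected, because readers will use it to interpret the result.

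**What to change.** Correct the Sample size section and leave enrolment as it is.

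1. State that 150 enrolled (135 evaluable after 10% loss) gives about 56% power for the three-group chi-square test at α 0.05 under 65%, 55% and 40%.
2. Say that this figure refers to neurological recovery, so that it is not taken as the power for a primary outcome.
3. Add the unadjusted pairwise powers at 45 per arm: about 67% for nCPAP vs standard, 29% for HFNC vs standard and 16% for nCPAP vs HFNC.
4. State that 90% power under these rates would have needed about 332 enrolled (333 with equal arms).
5. If other rates, another effect size or another contrast were entered in PASS, print those inputs with the power they give for 50 per arm, in place of items 1, 3 and 4.

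The cost is a few sentences and a less favourable stated power. No patients are added, and no analysis or procedure changes.

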### Randomisation and blinding

All participants are informed of the trial's purpose and sign an informed consent form. Participants will be randomised by block randomisation in the randomisation tool (www.randomisation.com). The randomisation sequence is assigned by an independent statistician using a random block size of 6 and 9 in a 1:1:1 fashion. The randomised numbers are placed in opaque sealed envelopes, and participants entering the group will be randomly given one of the envelopes and a grouping result based on the number. The data analysts in this study will not be involved in any interventions and will remain blinded to group allocation. The trial is open, as the researcher and participants cannot mask group allocation.

### Control group

In the trial, participants in the control group are treated with either conventional nasal cannula oxygen therapy or mask oxygen therapy. Treatment and care remained the same, except that the oxygen therapy is administered differently from the intervention groups. Participants will be monitored during their stay in the hospital and withdrawn from the clinical trial if necessary.

### Intervention groups

Participants in the intervention groups will be randomised to HFNC oxygen therapy and nCPAP oxygen therapy. In participants treated with HFNC oxygen therapy, the initial flow rate is set at 20L/min. Titration is performed during sleep, with each flow rate increasing by 10L/min until 60L/min, attempting to eliminate apnea, hypopnea, and hypoventilation in the supine position or during rapid eye sleep. When participants are treated with nCPAP, initial pressure support of 6-8cmH_2_O is first provided via a nasal mask. The nCPAP pressure is titrated and adjusted during sleep until apnea, hypopnea, and hypoventilation are eliminated. During titration, participants were sleep monitored using full-night polysomnography, and the number of apnea episodes, hypopnoea and hypoventilation episodes were recorded. When participants have completed titration, the setting of the optimal oxygen therapy mode parameters is recorded. Participants will be continuously ventilated according to the optimal oxygen therapy mode at the time of titration during their hospital stay. Participants will be monitored for changes in condition and oxygen saturation during the implementation of both interventions, and clinical trials will be terminated when necessary.

### Study outcomes

#### Primary outcomes

1. 28-day mortality rate; 2. Tracheal intubation rate (Rate of tracheal intubation in each group after one week using different ventilation methods); 3. Pulmonary infection rate (Rate of pulmonary infections in each group after one week using different ventilation methods).

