**ASSESSMENTS:**							
**Baseline questionnaire**	X						
**Follow-up questionnaire**			X	X	X	X	
**Analyse data**							X

*t*_*1*_: treatment in hospital

*t*_*2*_: 1 week after discharge

*t*_*3*_: 1 month after discharge

*t*_*4*_: 3 months after discharge

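### Tracheal intubation and pulmonary infection, two of the three primary outcomes, are timed by a week of device use and not from randomisation, so who is counted and over which days can depend on treatment received

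*Protocol article*

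**What the plan says.** All from the protocol article.

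- **Primary outcomes.** Intubation is the "Rate of tracheal intubation in each group after one week using different ventilation methods". Pulmonary infection is the "Rate of pulmonary infections in each group after one week using different ventilation methods". The third primary outcome is the "28-day mortality rate", which has a fixed length not tied to device use, although its time zero is not stated either.
- **Abstract, Methods.** "Patients receive different types of ventilation after admission to the group, and their tolerance while using the different ventilation is recorded". No interval between allocation and first use is given.
- **Intervention groups.** For HFNC, "Titration is performed during sleep, with each flow rate increasing by 10L/min until 60L/min". For nCPAP, "The nCPAP pressure is titrated and adjusted during sleep until apnea, hypopnea, and hypoventilation are eliminated". No limit on the duration of titration is stated. Afterwards, "Participants will be continuously ventilated according to the optimal oxygen therapy mode at the time of titration during their hospital stay".
- **Control group.** Conventional oxygen by cannula or mask; no titration is described.
- **Withdraw criteria and Adverse events.** Patients may leave the trial for intolerance and are withdrawn on deterioration.
- **Missing data plan.** Complete cases are used if fewer than 10% of participants are missing, and multiple imputation otherwise.
- **Discussion.** Some patients are said to comply poorly with CPAP because of airflow pressure and to be unable to use it for long.
- **Table 1.** The time points are treatment in hospital (t1, undated), "1 week after discharge", and one and three months after discharge.

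**The concern.** In a randomised comparison, the time origin and the set of patients counted should be fixed before treatment can influence them. A window defined by use of the device does neither. Where use starts, whether it lasts a week and why it stops are all post-randomisation matters, and each may differ between a titrated mask, a titrated high-flow cannula and ordinary oxygen.

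The link with the event itself makes this sharper. A patient intubated on day 3 has not had a week on the allocated device and may also meet the deterioration rule for withdrawal. If withdrawn patients are then handled as missing and complete cases are used, patients could be removed because they had the event. The trial is open-label, so a start or stop left to interpretation is also exposed to judgement. Two of the three primary outcomes are affected.

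**Working it through.** **Is there a figure to reproduce?** No. The document gives no expected rate for intubation or infection and no start delay. The sample size of 150 rests on neurological recovery and does not enter here, except that 150/3 = 50 patients per arm.

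**Step 1: when can the window open?** In the control arm there is one natural start, the first application of oxygen. In the other two arms there are two: first application, or use at the setting found by titration. The text fits either. It refers to use without saying at which setting, and device use plainly begins before titration is complete.

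**Step 2: when can it close, and who is counted?** Stopping, intubation, discharge and withdrawal can each end use before day 7. No sentence says whether such patients are events, non-events or excluded. The Missing data plan uses complete cases below 10% missing, that is, fewer than 0.10 × 150 = 15 participants. The document does not say that withdrawn patients count as missing, but nothing prevents it. If 10% to 30% of each arm were discharged before day 7 (assumed), 0.10 × 50 = 5 to 0.30 × 50 = 15 patients per arm would have an in-hospital window shorter than a week. Their events up to discharge would still be observed.

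**Step 3: what could a shifted window do?** Illustration only. Assume no treatment effect and a true risk R over days 0 to 7, with H = −ln(1 − R).

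*(a) Whole 7-day window starts d days late, hazard halving every h days.* The cumulative hazard in the window becomes H × 2^(−d/h), so the observed risk is 1 − exp(−H × 2^(−d/h)).

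For R = 15% and h = 2: H = 0.1625. With d = 1, 0.1625 × 0.7071 = 0.1149, giving 10.9%. With d = 2, 0.1625 × 0.5 = 0.0813, giving 7.8%.

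| True R | h = 2, d = 1 | h = 2, d = 2 | h = 3, d = 1 | h = 3, d = 2 |
|---|---|---|---|---|
| 10% | 7.2% | 5.1% | 8.0% | 6.4% |
| 20% | 14.6% | 10.6% | 16.2% | 13.1% |

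With a constant hazard, shifting a window of fixed length changes nothing.

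*(b) Counting from randomisation to seven days after a start delayed by d days, constant hazard.* Risk = 1 − (1 − R)^((7 + d)/7). For R = 20% and d = 1, 2, 3: 22.5%, 24.9%, 27.3%.

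*(c) Counting stops d days early, constant hazard.* Risk = 1 − (1 − R)^((7 − d)/7). For R = 20% and d = 1, 2, 3: 17.4%, 14.7%, 12.0%.

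A delayed start therefore lowers the apparent risk under (a) and raises it under (b), while early stopping lowers it under (c). If the same thing happens in all arms, no arm is favoured.

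**Step 4: the strictest reading.** If a completed week of use were required, an intubation that ended use before day 7 would leave both numerator and denominator. With R = 20%, 0.20 × 50 = 10 events per arm. Removing all of them gives (10 − 10)/(50 − 10) = 0% in every arm. That cannot be what is meant, but the wording does not exclude a partial version of it.

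**The case against.** The strongest answer is that the phrase is simply loose wording for status at one week on the allocated modality. It speaks of the rate in each group, which points to allocation, and the secondary outcomes use similar one-week phrases for NIHSS and AHI as plain time labels. On that reading an intubation on day 3 is an event. Nothing requires a completed week, and HFNC and nCPAP are already in use while being titrated, so all arms could start together. The 28-day mortality outcome has no stated time zero either, which suggests an abbreviated article whose full protocol or analysis plan may settle counting rules.

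Much of this stands. The benign reading is available and may be the intended one. It does not remove the point, because the article does not merely omit the window. It states one, and ties it to use.

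Three stronger inferences are tempting, and the document does not support them:

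- *That the definition favours HFNC and nCPAP.* Step 3 shows movement in both directions. Conditioning on a week of use removes early events from the control arm as well, so a bias needs stopping to differ by arm, by an amount the document does not give.
- *That the clock does start later in the active arms.* This is one reading; no section states a delay that differs by arm.
- *That Table 1 contradicts the outcome definition.* It has no dated one-week treatment visit, but its in-hospital time point can contain a day-7 assessment.

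**Conclusion.** The point holds as a weakness in how two of the three primary outcomes are defined. As written, the window depends on exposure, its start is open in two arms and not in the third, and the handling of patients who do not complete a week of use is unstated. The withdrawal rules and the expected difficulty with CPAP make it plausible, though not shown, that this would differ by arm.

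Any bias is of unknown direction and its size cannot be computed from the document. The percentages in the working rest on assumed risks of 10% to 20%, assumed delays or early stops of one to three days, and assumed hazard shapes. They show that the choice of window can matter by several percentage points, not that it does so here. If all devices start promptly after allocation and the authors count every patient at one week, the practical effect is small. This is a cheap improvement to make, not a demonstrated bias.

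**What to change.** Under Primary outcomes, define both as the cumulative incidence of a first tracheal intubation, and of a first pulmonary infection, from randomisation through day 7. State that they are counted by allocated arm in all randomised patients, whatever their device use, titration, stopping or withdrawal from treatment.

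For patients discharged before day 7, obtain event status and dates at the telephone contact already planned one week after discharge. Discharge on day x places that call on day x + 7, which is never before day 7, so it covers the whole window. Dating a day-7 assessment within the in-hospital time point of Table 1 would make the schedule explicit.

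**Cost.** A change of wording, with ethics approval if it falls under the article's rule on modifications. No treatment changes and no extra contact is needed. In-hospital event dates should be available from hospital records, which is a reasonable assumption but is not stated. The downside is that a few post-discharge events rest on telephone report. The stated timeline puts data analysis at close-out in August 2023, after the article's publication in June 2023, so the definition could still be fixed before analysis. Where the one-week call has already been made, the dates must come from what was recorded then or from a later planned contact.
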